#### Sample size and sampling method

2.2.1

According to the suggestion of Nunnally and Bernstien, selecting 5–10 participants per item is appropriate for multivariate analysis (46) 165 participants will be recruited to unitize the factor analysis for the 33 items of the Scale of Adherence to Cardiac Rehabilitation scale (ACRS). Considering a follow-up attrition rate of 20%, this number will increase to 198.

Following the approval of the research project by the Ethics Committee of the two hospitals, the study will be conducted on 198 participants with AMI after PCI one month after discharge who receive home-based OCR. The researchers will visit two hospitals, identify eligible patients using the hospital information system (HIS) following the proportion (70% and 30%) of the target population in two hospitals, explain the study objectives and brief process to them, and obtain informed consent to participate. Patients will complete the Demographic Data Sheet (DDS).

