Numerous benefits have been empirically supported and thoroughly demonstrated (13, 17, 18). These benefits include cardiac risk prevention (19), reduction of cardiac and all-cause mortality rates by approximately 30% and 15% at 1-year follow-up (14), and improvement of quality of life (QoL) and negative emotions (14, 20). However, hospital-based CR participation rates among eligible outpatient patients globally remain at a low level of 10%–30%, due to obstacles such as low socio-economic position, accessibility, conflicting commitments, and cost (21). As a result, home-based CR has gained popularity in the UK, Canada, and Australia, and the adherence rate of STEMI-PCI patients to OCR has remained between 22% and 80% (22, 23). However, this situation is not optimistic in China. The adherence rate has only reached 7.05%–29.9% (24, 25), although the rate among inpatients was 72.74% (26). Chinese scholars have released a summary of multiple pieces of evidence related to CR (27, 28) and have suggested that patients in stable conditions can more flexibly switch to home-based CR from hospital- or center-based CR to improve adherence with appropriate self-monitoring methods.

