##### The scale of adherence to cardiac rehabilitation (ACRS)

2.2.4.6

The ACRS was developed by Wen, X.H. (52) based on quality interviews and literature reviews to assess adherence to CR in CHD patients. The ACRS contains 33 items with five subscales: exercise, medication, risk factors, nutritional, and psychological management. The I-CVIs of the scale ranged from 0.80–1.00, while the S-CVI was 0.96. The cumulative variance contribution rate was 60.698%, and the CFA showed good structural validity: *X*^2^ < 0.001, RMSEA = 0.055, CFI = 0.851 (52). The scale responds “yes” or “no” for each item (yes = 1 point, no = 0 points). The total score range of the scale is 0–33 points. The total score is classified into high and low: 33–25 points indicates high adherence to cardiac rehabilitation and 24–0 indicates low adherence to cardiac rehabilitation (45).

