#### Data analysis

2.2.6

IBM SPSS 22.0 software will be used for data analysis. Statistical significance will be set at *p* < 0.05. The data analysis process was as follows:

The independent variables, including demographic variables, psychological characteristics, and the six constructs of the HBM, are described using frequency, percentage, mean, and standard deviation.

Dummy coding will be performed for categorical data. The assumption of logistic regression, including linearity, homoscedasticity, and residual normality, will be checked before entering the data into SPSS. Linearity: The partial regression plot between dependent and independent variables should be random. Homoscedasticity: Check the residual plot of the dependent variable; the scatter plot should be random without a curve pattern. Normality of residuals: Check the histogram of the dependent variable and a standard probability plot. Univariate analysis and binary logistic multivariate statistical analysis will be used to calculate the regression coefficient, odds ratio (OR), and 95% confidence interval of each variable using the stepwise entry method, and the independent risk factors related to adherence to home-based phase 2 CR will be analyzed.

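### The sample size rests on a factor analysis that the plan does not contain, and the planned stepwise logistic regression has at most about 4 to 5 events per candidate parameter

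*Protocol article*

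**What the plan says.** Section 2.2.1 cites a rule that "selecting 5–10 participants per item is appropriate for multivariate analysis". It applies the lower end of that rule to the items of the outcome scale: "165 participants will be recruited to unitize the factor analysis for the 33 items". It then adds an allowance: "Considering a follow-up attrition rate of 20%, this number will increase to 198". No other basis for the size is given.

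Section 2.2.6 plans descriptive statistics and then regression: "Univariate analysis and binary logistic multivariate statistical analysis will be used to calculate the regression coefficient, odds ratio (OR), and 95% confidence interval". Variables are to be entered stepwise and categorical ones dummy coded. No factor analysis is listed.

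The predictors are set out in the same section: "The independent variables, including demographic variables, psychological characteristics, and the six constructs of the HBM, are described". The outcome is the ACRS total, cut in section 2.2.4.6: "33–25 points indicates high adherence to cardiac rehabilitation and 24–0 indicates low adherence to cardiac rehabilitation".

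The first objective in section 1.2 is the level of adherence and the factors that influence it. None of the three objectives is to validate a scale.

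**The concern.** A rule that counts patients per questionnaire item is meant for studying the structure of a scale. Here the ACRS is only scored and split at 25 points, and its validity figures come from earlier work. The rule therefore does not tell the reader how precisely the adherence proportion will be estimated, or how large a logistic model the data can carry.

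For a logistic model the limiting quantity is the number of patients in the smaller outcome class, set against all parameters that compete for entry. Univariate screening and stepwise entry do not reduce that count, because a variable that has been screened out was still a candidate.

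With few events per candidate, the selected set can change with small changes in the data, and the odds ratios of the survivors tend to be exaggerated. The design is sequential, so this would not stay in phase one. Section 2.3.2 builds the interview guide on the quantitative findings, and section 2.4 derives the proposed strategies from the earlier phases.

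**Working it through.** **1. The plan's own figures.** 5 × 33 = 165, as stated. 165 × 1.20 = 198, as stated. Losing 20% of 198 leaves 198 × 0.80 = 158.4, so the number analysed could lie anywhere from about 158 to 198. All results below are given over that range or at the target of 165.

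**2. Candidate parameters**, counting one for each named variable:
- Demographic (2.2.4.1): age, sex, marital status, education, employment, smoking = 6
- History of illness (2.2.4.1): diabetes, dyslipidemia, length of stay, D2B time, arrhythmia during PCI = 5
- HBM constructs (2.2.6), read as the five dimensions of the health belief scale (2.2.4.4) plus self-efficacy (2.2.4.5) = 6
- Depression (2.2.4.2) and social support (2.2.4.3) = 2

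Total: 6 + 5 + 6 + 2 = 19. This is a minimum. Both lists in 2.2.4.1 are given as examples, and dummy coding adds a parameter for each level beyond two.

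**3. Events per candidate** = N × min(p, 1 − p) / 19, where p is the share with high adherence. The protocol gives no p for its own sample. The scenarios are the Chinese range in the Background ("The adherence rate has only reached 7.05%–29.9" per cent), the range in its sentence on home-based rehabilitation abroad ("the adherence rate of STEMI-PCI patients to OCR has remained between 22% and 80" per cent), and the best possible case, p = 50%.

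| p (assumed) | Smaller class at N = 165 | Per candidate, N = 158 | N = 165 | N = 198 |
|---|---|---|---|---|
| 7.05% | 11.6 | 0.59 | 0.61 | 0.73 |
| 22% | 36.3 | 1.83 | 1.91 | 2.29 |
| 29.9% | 49.3 | 2.49 | 2.60 | 3.12 |
| 50% | 82.5 | 4.16 | 4.34 | 5.21 |
| 80% | 33.0 | 1.66 | 1.74 | 2.08 |

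Over 22% to 80% at N = 165 the ratio runs from 1.7 (at 80%) to 4.3 (at 50%). If dummy coding brought the count to 25 (an assumption), N = 165 would give 0.47 at 7.05%, 1.97 at 29.9% and 3.3 at 50%.

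**4. What 165 patients can carry.** Ten events per parameter is a common benchmark. It is an outside assumption and is not in the protocol. By it, the smaller class supports 11.6/10 ≈ 1, 49.3/10 ≈ 5 or 82.5/10 ≈ 8 parameters at 7.05%, 29.9% and 50%. Carrying all 19 would take 19 × 10 / 0.50 = 380 patients even at an even split.

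**5. What 165 patients deliver for the adherence level.** The 95% half-width is 1.96 × √(p(1 − p)/165):
- p = 50%: 1.96 × √(0.2500/165) = 0.076, the maximum
- p = 29.9%: 1.96 × √(0.2096/165) = 0.070
- p = 7.05%: 1.96 × √(0.0655/165) = 0.039

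**The case against.** The strongest reply is that the low figures depend on borrowed rates. The Background does not say how the 7.05% to 29.9% was measured. This study enrols only patients already taking part in home-based rehabilitation (2.2.2), and the ACRS also covers medication, nutrition, risk factors and psychological management. The share scoring 25 or more could be quite different. This stands: 0.6 to 2.6 is a scenario, and a reader should not take it as the ratio the study will have. It does not rescue the plan, because the 50:50 ceiling uses none of these rates.

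A reader might also infer that the odds ratios are certain to be biased, or that separation is likely. The protocol does not support either. No separation probability was calculated, and that worry attaches mainly to 7.05%, the least secure scenario for this sample. What can be said is that there is a risk. Nor is the choice of interviewees compromised: section 2.3.1 selects them by extreme ACRS scores, not by the regression.

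Finally, this is a condensed article, and a power or events-per-variable argument may sit in a fuller document. Its absence is not the point here. The point is that the basis the article does state belongs to an analysis it does not plan.

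**Conclusion.** The point holds. The mismatch between 2.2.1 and 2.2.6 can be read directly from the text and needs no assumption. The overload of the logistic model follows from at least 19 named candidates: at most about 4.2 to 5.2 events per candidate at an even split, and fewer with any other split or with dummy coding. The lower figures (0.6 to 2.6, or 1.7 to 4.3) rest on assumed adherence rates and should be labelled so.

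This weakens the part of objective 1 that concerns influencing factors, and what phases two and three draw from it. It does not make the study infeasible, and the adherence level remains estimable with useful precision. The change should be made, but it does not call for more patients.

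**What to change.** **Section 2.2.1, same number of patients.** Replace the factor-analysis sentence with what the size delivers for the planned analyses. Give the 95% half-width for the adherence proportion at 165 patients: at most ±7.6 points at 50%, with ±7.0 at 29.9% and ±3.9 at 7.05% as assumed scenarios. Add the number of parameters the model can support, naming any events-per-parameter benchmark as an outside assumption.

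**Section 2.2.6.** Replace stepwise entry with a pre-specified model fitted by penalised logistic regression (Firth or ridge). Put the six HBM constructs in first. Let the investigators rank further covariates from prior evidence, and admit them only as far as the size of the smaller outcome class allows. That size can be read without looking at any predictor, so the rule can be fixed in advance. Report the remaining variables descriptively or as exploratory.

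The six constructs alone would have 82.5/6 = 13.8 events each at 50:50, 49.3/6 = 8.2 at 29.9% and 11.6/6 = 1.9 at 7.05% (N = 165). Penalisation is therefore needed in any case, and if very few patients fall in one class the model should be presented as exploratory.

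**Cost.** Two sections are reworded. Fewer variables get an adjusted estimate, and penalised fitting may need software other than SPSS 22.

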**Methods:**

An explanatory sequential mixed-methods design will be employed to conduct this study with three phases. The first phase is a quantitative study with a cross-sectional design to assess the level of adherence to outpatient cardiac rehabilitation and related influences based on the Health Belief Model among 198 patients with ST-elevation myocardial infarction after percutaneous coronary intervention in two tertiary hospitals in Zhenjiang, Jiangsu Province, China. The second phase is followed by a qualitative study to explore the patients’ perceived facilitators and barriers to adherence to outpatient cardiac rehabilitation. Purposive sampling, semi-structured interviews, and conventional content analysis approaches will be used to collect and analyze the data. The final phase links to integrating the data and developing a targeted strategy to improve adherence to outpatient cardiac rehabilitation among patients with ST-elevation myocardial infarction after percutaneous coronary intervention. The nominal group technique and "weaving techniques" will be implemented in accordance with the results of the preceding two phases.

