### Phase one: quantitative study

2.2

Phase one is designed as a cross-sectional study that will be carried out to assess the level of adherence to OCR of STEMI-PCI patients one month after discharge from two tertiary hospitals in Zhenjiang, Jiangsu Province, China. Then, the impact of demographic variables, psychological characteristics, health beliefs, and adherence to OCR, as well as the related factors influencing adherence, will be investigated.

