#### Data collection

2.2.5

This study will collect quantitative data using questionnaires. The following stages will be implemented to complete the data collection process.
(1)After obtaining permission from the directors of each hospital, the researcher will ask one research coordinator from the cardiac clinic of each hospital and a quiet, private room at the cardiac clinic to collect the form and questionnaires.(2)The researcher will prepare 200 packages, each containing a form and five questionnaires, and explain the data collection process to the research coordinators.(3)The researcher will obtain a list of STEMI PCI patients for follow-up at the outpatient department. The researcher will screen eligible patients and assign numerical codes to replace the patients' names. Subsequently, the researcher will provide a coded list to the research coordinators for subject selection.(4)The research coordinator will schedule an appointment in advance for potential patients at the cardiac clinic after they meet the doctor and explain the study's purposes, procedures, duration, and benefits. If the subjects agree to participate, they will be requested to sign a consent form.(5)The research coordinator distributes the research package to all participants. Each participant will spend 45–60 min completing the questionnaires and will then return the questionnaires and consent form separately in two designated boxes within the room. The research coordinator then checks for the completeness of all documents collected from the boxes and returns them to the researcher every week.

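### The 20% attrition allowance was added to 165 rather than divided out, so 198 recruited yields about 158 at that loss, slightly short of the plan's own target (minor arithmetic error)

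*Protocol article*

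**What the plan says.** All the figures for this calculation are printed in the protocol article.

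- Section 2.2.1 (Sample size and sampling method) gives the rule: "selecting 5–10 participants per item is appropriate for multivariate analysis".
- It applies the rule to the adherence scale: "165 participants will be recruited to unitize the factor analysis for the 33 items". The item count agrees with section 2.2.4.6, where "The ACRS contains 33 items with five subscales".
- It then makes the allowance for loss: "Considering a follow-up attrition rate of 20%, this number will increase to 198".
- The result is carried forward as the study size. Section 2.2.1 says that "the study will be conducted on 198 participants with AMI after PCI one month after discharge who receive home-based OCR", and the abstract's Methods paragraph describes a survey "among 198 patients with ST-elevation myocardial infarction after percutaneous coronary intervention in two tertiary hospitals".
- Section 2.2.5 (Data collection) sets the supply of questionnaires to match: "The researcher will prepare 200 packages".

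The article gives no other formula for the allowance and no other sample size criterion.

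**The concern.** An allowance for attrition exists so that the target number remains after the loss. The rate applies to those recruited, so the target has to be divided by the share who stay. Multiplying the target by one plus the rate gives too small a number, because the 20% is then lost from the larger group.

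The slip shows here because the target has no slack. The plan chose five per item, the bottom of its own range. With six or seven per item, the same slip would still have left more than five. At five, a loss at the planned rate takes the study below both the 165 it set and the range it cites in support. A reader who relies on 198 as covering a 20% loss would be relying on a yield that the figure does not give.

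**Working it through.** **Inputs**

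- Items on the adherence scale: 33 (sections 2.2.1 and 2.2.4.6).
- Participants per item: 5–10 (section 2.2.1).
- Target before the allowance: 165 (section 2.2.1).
- Attrition rate: 20% (section 2.2.1).
- Number to be recruited: 198 (section 2.2.1 and abstract).

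**Step 1. Reproduce the plan's figures.**
Target: 33 × 5 = 165. The top of the range would be 33 × 10 = 330.
Allowance as target × (1 + rate): 165 × 1.20 = 198.
Both figures are reproduced exactly, so the method used is clear.

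**Step 2. Apply the stated loss to 198.**
Remaining = recruited × (1 − rate): 198 × 0.80 = 158.4, about 158.
Shortfall against the target: 165 − 158.4 = 6.6, about 7 people.
Per item: 158.4 / 33 = 4.8, against a lower end of 5.

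**Step 3. Find the loss that 198 does cover.**
1 − 165/198 = 0.167, that is 16.7%.

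**Step 4. Find the number that a 20% loss would require.**
165 / (1 − 0.20) = 206.25, rounded up to 207.
Check: 207 × 0.80 = 165.6, which keeps 165; 206 × 0.80 = 164.8, which does not.
Difference from the plan: 207 − 198 = 9, or 4.5% of 198. This is not rounding.

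**Step 5. Gauge the effect on precision.**
To a first approximation, the width of a confidence interval goes with one over the square root of the sample size. √(165/158.4) = 1.02, so intervals would be about 2% wider than with 165.

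**The case against.** Several things can be said for the plan.

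**The 20% might be a recruitment margin.** On that reading 165 × 1.20 is correct. But the text calls it an attrition rate. The same sentence sequence also speaks of recruiting 165, yet an allowance for loss has no purpose unless 165 is the number meant to remain. This objection does not stand.

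**The consequence is small.** This stands. The shortfall is about 7 people, or 0.2 per item, against a rule of thumb. The rule is tied to a factor analysis of the scale, whereas section 2.2.6 sets out univariate analysis and binary logistic regression and describes no factor analysis. Falling just under five per item therefore does no identifiable harm to the analysis described.

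**The shortfall is conditional.** This also stands. It arises only if the loss exceeds 16.7%, and the article reports no observed loss rate. What is wrong is the statement that 198 covers 20%.

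A reader might also infer that the term for the loss is wrong, since section 2.2 says "Phase one is designed as a cross-sectional study" and questionnaires are completed at one clinic appointment. The article does not support that. Section 2.2.5 draws patients from an outpatient follow-up list and books appointments in advance, so non-attendance is a possible source of loss that the term may loosely cover.

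A reader might likewise count the 200 packages as a second error. They are consistent with 198 participants and would fall short only if 207 were adopted.

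**Conclusion.** The sample size statement in section 2.2.1 is arithmetically wrong as written. At the stated 20% loss, 198 recruited gives about 158, or 4.8 per item, and not the 165 and 5.0 per item that the allowance was meant to secure. It secures them only up to a loss of 16.7%.

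This rests on two readings, both of which follow the text: that the 20% is a proportion of those recruited, and that 165 is the number to be kept. It needs no figure from outside the article.

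The error is minor. A reader might infer that the study is underpowered or must enrol 207. The article does not support that: it states no power, precision or effect target that 158 would miss, and 207 would only preserve a base of 165 that has no stated link to the planned regression. The number 207 is what the plan's own assumptions imply, not a size shown to be needed.

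**What to change.** Restate the yield in section 2.2.1, in one of two equivalent ways:

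- 198 recruited is expected to give about 158 complete sets at a 20% loss, which is 4.8 per item; or
- 198 recruited supports 165 complete sets, five per item, provided that the loss is at most 16.7%.

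Either is a change to one sentence. The abstract's 198 and the 200 packages in section 2.2.5 can stay, and the term used for the loss need not change. The cost is a slightly less favourable stated yield.

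If the investigators prefer to keep both 165 and 20%, the number becomes 207, with the abstract and sections 2.2.1 and 2.2.5 changed to agree and at least 207 packages prepared. That is optional.

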Despite the general recognition of the benefits of CR adherence, dropout rates exceed 80% (29, 30). Numerous studies have shown a significant increase in the risk of death and MI when CR programs are not adhered to (13), and the influencing factors are multifactorial and individualistic (31). According to an Australian study, the factors included male sex, employment status, health support, shorter hospital stays, and previous AMI or PCI (23). However, in China, adherence was adversely correlated with age, male sex, hyperlipidemia, and D2B time, but positively connected to educational level and arrhythmia during PCI (25). Additional research has noted that adherence to OCR is statistically influenced by patient recognition (32), depression (33, 34), and self-efficacy (35, 36). Diabetes, smoking, and CR costs (22, 37) were all linked to poor OCR adherence. A qualitative study found that STEMI-PCI patients may not be able to recognize and manage ischemic symptoms immediately, may have psychological problems during the acute and recovery stages (38), as well as often overestimate their level of physical activity after discharged (39). More importantly, few studies have investigated effective strategies for improving the level of adherence to OCR in STEMI-PCI patients. The identification of both facilitators and obstacles to adherence to OCR and the mechanisms involved have not been evaluated.

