#### Exclusion criteria

2.2.3

Patients who (1) have complications from PCI and (2) participate in the phase 2 CR program in the hospital as outpatients will be excluded.

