##### The demographic data sheet (DDS)

2.2.4.1

The researcher will develop a DDS, which will include two parts: demographic data, such as age, sex, marital status, educational level, employment status, and smoking status, and history of illness, such as diabetes, dyslipidemia, length of stay, D2B time, and arrhythmia during PCI. The DDS will be a form of open-ended and closed-ended questions.

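### Door-to-balloon time and arrhythmia during PCI are collected on a form that patients fill in, although patients cannot be expected to report either reliably

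*Protocol article*

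**What the plan says.** Protocol article, section 2.2.1 (Sample size and sampling method): after consent, "Patients will complete the Demographic Data Sheet (DDS"). The same section has the researchers "identify eligible patients using the hospital information system (HIS"), which is the only use of hospital records that the article describes for this phase.

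Section 2.2.4.1 (The demographic data sheet): the second part of the sheet covers "history of illness, such as diabetes, dyslipidemia, length of stay, D2B time, and arrhythmia during PCI". On format: "The DDS will be a form of open-ended and closed-ended questions".

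Section 2.2.5 (Data collection): "This study will collect quantitative data using questionnaires". The participant receives a package, "each containing a form and five questionnaires", and returns the completed material in boxes. The coordinator then checks that the documents are complete.

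Section 1 (Background): an earlier Chinese study is reported to have found adherence negatively related to D2B time and "positively connected to educational level and arrhythmia during PCI".

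Section 2.2.3 (Exclusion criteria) removes patients who "have complications from PCI". The term is not defined.

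**The concern.** D2B time is an interval that the hospital records, and an arrhythmia during PCI is a finding of the procedure. Both belong to the medical record. A patient asked about them a month after discharge, by questionnaire, will often guess or leave the answer blank. A completeness check cannot tell a wrong answer from a right one, and pressure to complete the form may turn blanks into guesses.

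What is at stake is limited but real. The first objective is to determine which factors influence adherence, and section 2.2.6 takes candidate factors through univariate analysis and stepwise logistic regression. A badly measured factor tends to show a weak association and to drop out of a stepwise model. A null result for D2B time or arrhythmia could then be read as contradicting the earlier Chinese finding when it reflects only the data source.

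**Working it through.** **Step 1. Is patient report actually stated?** The places side by side:

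| Question | Where | Answer |
|---|---|---|
| Who completes the sheet? | 2.2.1 | The patient |
| What is on it? | 2.2.4.1 | D2B time and arrhythmia during PCI, among others |
| What kind of form? | 2.2.4.1 | Open and closed questions |
| How are quantitative data collected? | 2.2.5 | By questionnaire |
| What is in the package? | 2.2.5 | One form and five questionnaires |
| What are hospital records used for? | 2.2.1 | Identifying eligible patients |

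Sections 2.2.4.2 to 2.2.4.6 describe exactly five scales, so the one remaining form in the package fits the demographic data sheet. Patient report is therefore a stated choice of data source.

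**Step 2. Which items are affected?** D2B time and arrhythmia during PCI clearly are. Diabetes, dyslipidemia and length of stay are things that a patient can reasonably report.

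**Step 3. Size.** The plan gives no figure on recall accuracy, blanks or effect size, so there is nothing to reproduce. What follows shows only how the mechanism works. The figure 165 is from section 2.2.1; every other input is an assumption.

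*D2B time.* Assume classical measurement error, a true odds ratio (OR) of 1.5 per SD, and reliability λ between 0.3 and 0.6. To a first approximation the log OR is multiplied by λ if the unit is one SD of true D2B time, and by √λ if the unit is one SD of the recorded value.

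| λ | Per SD of true D2B: 1.5^λ | Per SD of recorded D2B: 1.5^√λ |
|---|---|---|
| 0.3 | 1.13 | 1.5^0.548 = 1.25 |
| 0.6 | 1.28 | 1.5^0.775 = 1.37 |

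*Arrhythmia during PCI.* Assume 165 analysed, 15% truly exposed (about 25 patients), 30% high adherence among the unexposed, a true OR of 2.5, and errors in reporting unrelated to adherence. High adherence among the exposed is then odds 0.30/0.70 × 2.5 = 1.071, or 51.7%. With sensitivity Se and specificity 0.95:

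- share reported as exposed = 0.15·Se + 0.85·0.05
- high adherence among those reported exposed = (0.15·Se·0.517 + 0.85·0.05·0.30) / share reported as exposed
- high adherence among those reported unexposed = (0.15·(1 − Se)·0.517 + 0.85·0.95·0.30) / (1 − share reported as exposed)

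For Se = 0.5 the share is 0.1175, the two proportions are 0.439 and 0.318, and the observed OR is (0.439/0.561)/(0.318/0.682) = 1.67. Power is for a two-sided 0.05 comparison of two proportions by normal approximation.

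| Reporting | Observed OR | Power |
|---|---|---|
| Perfect | 2.50 | 0.56 |
| Se 0.8, Sp 0.95 | 1.92 | 0.34 |
| Se 0.5, Sp 0.95 | 1.67 | 0.19 |
| Se 0.3, Sp 0.95 | 1.45 | 0.11 |

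*Blanks.* The article does not say how missing predictor values are handled. If complete cases were used and 20% to 40% left D2B time blank (both assumed), a model containing it would lose 0.2 × 165 = 33 to 0.4 × 165 = 66 patients.

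**Step 4. The exclusion.** Section 2.2.3 removes patients with PCI complications; section 2.2.4.1 records arrhythmia during PCI as a factor. The wording differs, and nothing in the article equates the two or separates them.

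**The case against.** The data-source point rests mainly on one sentence in a sampling section of a condensed article. The sheet is still to be developed. Section 2.2.5 lists the form separately from the questionnaires, and describes participants completing the questionnaires without naming the form. The full protocol might have staff fill in the clinical part. This leaves some room, but not enough: the article says outright who completes the sheet and what is on it, and nowhere says that the clinical part comes from records.

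It is also fair that section 2.2.6 describes the independent variables as demographic, psychological and Health Belief Model variables, without naming D2B time or arrhythmia, and that most factors in the Background are unaffected. This limits the point to two variables. It does not remove it, because the sheet collects both and the Background gives the reason.

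Three stronger readings are tempting, and the documents do not support them:

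- **That the two factors cannot be measured at all.** The team already uses the hospital information system, so the weakness lies in the source chosen and is easily remedied.
- **That the exclusion removes the arrhythmia cases.** That depends on an undefined term. Since the authors plan to record intra-procedural arrhythmia, they may well not regard it as excluded. What remains is a request for clearer wording.
- **That the loss can be quantified.** Reliability, sensitivity, share of blanks and true effects are all assumed, complete-case deletion is not stated, and the D2B attenuation depends on which SD is the unit.

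**Conclusion.** The point holds for two variables. As written, D2B time and arrhythmia during PCI come from patient report, a poor source for both. Their associations with adherence would be biased or lost to blanks. The bias is typically toward the null if errors are unrelated to adherence; if adherent patients know their own records better, the direction is not assured. The judgement that patients cannot report these items reliably rests on the nature of the items, not on data in the article.

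The size cannot be derived from the documents, and the figures under the working are illustrations only. The adherence level itself and the other candidate factors do not depend on this. The change is worth making because it decides whether two factors that the Background names can be examined properly. The link with the exclusion criterion is a secondary clarification.

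**What to change.** In sections 2.2.1 and 2.2.4.1, split the sheet by source. The researcher extracts D2B time and arrhythmia during PCI from the hospital information system under the patient's code; length of stay and the diagnoses can conveniently be taken at the same time. The patient completes the social and lifestyle items. The consent form must cover access to the record for this purpose.

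Reconcile sections 2.2.3 and 2.2.4.1 by stating whether arrhythmia during PCI counts among the excluded complications, so that both hospitals screen alike. Which reading applies is for the investigators to decide. If it is excluded, it should not remain a candidate factor.

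The cost is a short chart extraction per patient, for up to 198 patients, by a team that already has access to the system, plus the consent wording and one clarifying clause.
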